**Figure 1 F1:**
[figure not shown]
**Trial flow diagram**.

### Trial conduct

Approach to patients and obtaining informed consent

Patients will be identified through upper GI cancer teams. Eligible patients will be invited to participate by their treating clinician, specialist clinical nurse or research nurse. If agreeable, written informed consent will be obtained, following a face to face discussion about the study.

#### Randomisation and drug / placebo supply

The trial statistician will produce the randomisation sequence using a block size of 10 with equal allocation between active and placebo groups. Drug (salmeterol 25 mcg metered dose inhaler) and matching placebo will be supplied and packaged according to the randomisation sequence into numbered treatment boxes by MODEPHARMA(London, UK). Drug boxes will be supplied in groups of ten to centres thus ensuring an equal allocation between active and placebo groups to balance any differences in case mix, pre-operative, operative and post-operative care between centres. Patients will be randomised sequentially by allocating them to the next numbered treatment pack held at the centre.

#### Drug administration

Subjects will receive either 100 mcg inhaled salmeterol or placebo via a spacer device within two hours of induction of anaesthesia and then 12 hourly for 72 hours. The drug will be administered by qualified medical or nursing staff. Whenever possible, subjects will be extubated at the end of surgery. Subjects requiring ventilation post operatively will receive 100 mcg of the drug via an in-line chamber inserted into the inspiratory limb of the ventilator circuit.

#### Concomitant medications

The following medications should not be prescribed to patients for the duration of the clinical study. Long acting beta agonists, non-cardioselective beta blockers (the cardioselective beta blockers atenolol, betazolol, bisoprolol and metoprolol are permitted) or another investigational medicinal product.

Inhaled or nebulised short acting beta agonists should be avoided whenever possible, but are permitted in this trial in the event of severe bronchospasm.

#### Post randomisation withdrawals and exclusions

Subjects may withdraw from the trial or the trial treatment at any time without prejudice. If a subject withdraws from the trial treatment, then they will be followed-up wherever possible and data collected as per protocol until the end of the trial. The only exception to this is where the subject also explicitly withdraws consent for follow-up.

#### Protocol compliance

Compliance with study drug administration will be recorded in the data collection booklet by the trial team by cross referencing with the subjects individual trial drug pack and drug treatment chart.

#### Blinding / un-blinding

Patients, clinical and research / trial staff will be unaware of which arm of the study a patient is allocated. Active and placebo treatment packs and their contents will be identical in appearance. The protocol allows for emergency un-blinding in the event of significant concerns about patient safety. In the unlikely event that un-blinding is required the local investigator will discuss with the Chief Investigator. All events will be logged.

#### Monitoring and reporting adverse events

Balti-prevention is recruiting a population who are prone to recognized medical and surgical complications. It is expected that many of the patients will experience an event that might be seen as a serious adverse event but is a recognized complication following oesophagectomy. Adverse and serious adverse events which are recognised complications of surgery e.g. medical (pneumonia, sepsis) and surgical (chyle leak, anastamosis leak) will be recorded in the case report form.

Death, other serious adverse events thought to be related to the study drug or serious unexpected serious adverse reactions will be reported to the trial co-ordinating centre and Chief Investigator within 24 hours of becoming aware of their occurrence who will inform the sponsor and regulatory authorities.

#### Data collection

Data up until hospital discharge will be recorded in each subject's Case Report Form (CRF) by hospital staff. Most of the data collected will be obtained from the patients hospital notes. In the unlikely event that a subject is transferred to another hospital, the study team will ensure that data collection is completed by the receiving hospital.

If the subject remains in hospital at 28 or 90 days, survival at these time points will be recorded by hospital staff. Mortality after hospital discharge will be obtained from NHS Statistical Tracing Service (NSTS).

Health related quality of life follow-up at 28 days and 90 days will use face to face interview if the subject is still in hospital or postal questionnaire. Any subject who has moved house without informing the trial team will be traced via the NHS Strategic Tracing Service. The questionnaire will contain the EuroQoL (EQ-5D) and resource use questions.

Postal questionnaires will be sent out and collected by WCTU. Questionnaires that are not returned, will be chased using a standard protocol involving reminders by post (2), telephone (2) and if necessary, collection of core data items by telephone.

### Statistical analysis plan

The primary analysis will be based on 'Intention-to-treat' (ITT). In the ITT analyses, patients will be analysed according to the treatment they were randomised to, irrespective of the treatment they actually received. In addition a per-protocol analysis will be conducted. Patients that did not proceed with planned surgery or did not receive the pre-operative dose of drug will be excluded.

Multiple imputation methods will be used to impute missing data. Prior to an imputation, the data mechanisms (MAR - missing at random; NMAR - not missing at random; MCAR - missing completely at random) will be assessed to make sure that multiple imputation is viable. Only data that is validly missing will be imputed. In the case of multivariate normal data, the multiple imputation methods assuming normality will be used. In the case where one cannot assume a distribution of the data, the ICE (imputation by chain equations) will be used. The imputed (intention to treat and adherence to protocol) datasets will be used for sensitivity analyses.

The primary outcome measure will be compared between treatment groups using a logistic regression model, with the dependent variable as acute lung injury/no acute lung injury within 72 hours and the independent variables as treatment and other important predictors (e.g. centre and age). An odds ratio measuring the treatment effect and its 95% confidence interval will be reported.

Categorical data will be analysed using logistic regression models, with treatment group as an independent variable along with other important predictors. The summary statistics will be based on proportions and the 95% CI. Continuous data: Continuous data will be analysed using linear regression models, with treatment group as an independent variable along with other important predictors. Difference in treatment will be based on adjusted mean estimates and 95% CI's. Time to event data will be analysed using a log-rank test. Any patients who have not experienced an event at the time point of interest or withdrawn will be censored. The proportion experiencing an event over time will be illustrated using a Kaplan-Meier curve for each of the treatment groups. The p-values and a hazard ratio with its 95% CI from a Cox proportional hazards model will also be presented. The proportional hazard assumption across treatment arms will be checked graphically using a log-cumulative hazard plot.

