#### Secondary outcomes

The trial secondary outcomes are the development of ALI/ARDS during the first 28 days post operatively; PaO_2 _: FiO_2 _ratio; the number of ventilator and organ failure free days, 28 and 90 day survival; health related quality of life and resource utilisation.

Ventilator free days are defined in accordance with the ARDSnet criteria[23] as the number of calendar days after initiating unassisted breathing to day 28 after randomisation, assuming a patient survives for at least 48 consecutive hours after initiating unassisted breathing. Un-assisted breathing is defined as one of at least 48 consecutive hours of (1) being extubated with face mask, nasal prong oxygen, or room air (2) T-tube breathing (3)Tracheostomy mask breathing, CPAP = 5 cm H_2_0 without pressure support of intermittent mandatory ventilation assistance. For example, if a subject initiates unassisted breathing on day 16 and survives to day 28, he/she will be assigned a value of 12 VFDs. If a similar subject begins unassisted breathing on day 16 but dies on day 25, the VFDs is 9. If a subject survives for >48 consecutive hours of unassisted breathing but requires assisted breathing (for any reason) before day 28, he/she will be assigned only the number of days of unassisted breathing before day 28. Subjects who die without initiating unassisted breathing or before 48 consecutive hours of unassisted breathing will be assigned a value of zero VFDs. Subjects transferred to another hospital or other health care facility prior to day 28 (intermediate care, nursing home etc.) while still on positive pressure ventilation will be followed up to assess this efficacy measure.

Organ failure free days are defined in a similar manner to ventilator free days with an organ failure free day being a day without evidence of non-respiratory organ failure. Organ failure will be defined as a sequential organ failure assessment (SOFA) score of greater than 3[24].

Health related quality of life will be measured using EuroQol (EQ-5D). Data will be collected at baseline, 28 days and 90 days. Resource utilisation (intensive care and hospital length of stay) will be recording. The cost of intervention and resource use will be compared.

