### Power and sample size estimate

A systematic review of the literature noted significant variability in the incidence of acute lung injury after oesophagectomy with reports ranging from 14.5 - 43%[5]. Major studies relevant to the UK population include the national CEPOD report which quotes an incidence of 27%[8] and national gastro-oesophageal audit(ASCOTT) which had an incidence 40.5%[7]. An analysis of 6971 patients from Intensive Care National Audit and Research Centre (ICNARC) found that 3352 (47%) fulfilled the oxygenation criteria for ALI in the first 24 hours post operatively[6]. A 5 year audit of oesophagectomies at Heart of England NHS Trust identified that 28% of patients fulfilled criteria for ALI. Based on these data a conservative estimate of the incidence ALI of 25% was selected.

There are no prospective randomised controlled trials in oesophagectomy patients to predict the size of the treatment effect of salmeterol for preventing ALI. In the randomised controlled high altitude pulmonary oedema study, the prophylactic use of salmeterol reduced the incidence of pulmonary oedema from 74 to 33% (55% relative reduction)[13]. LPS challenge studies in humans have shown that salmeterol can reduce neutrophil influx, inflammatory cytokine production and aberrant coagulation by 40-66% relative reduction[12,27]. The study originally set out to demonstrate a 15% absolute reduction in development of acute lung injury. However the study funders requested in 2009 that the study was re-powered to detect a more modest treatment effect. The size of the treatment effect was decided following discussions with the British Society of Oesophageal Gastric Surgeons. Assuming a baseline incidence of lung injury of 25%, consensus was reached that a treatment effect of at least 12.5% (50% relative reduction) was necessary to convince clinicians to translate the treatment into clinical practise should the trial demonstrate that salmeterol prevents ALI/ARDS. This equates to a number need to treat of eight to prevent one episode of lung injury.

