To demonstrate this effect with 80% power at a significance level of 0.05 will require 336 patients. To ensure the study maintains sufficient power after drop-outs we have included a 5% failure to proceed to oesphagectomy / receive one lung ventilation and a 2.4% loss to follow-up rate[28]. This gives an overall sample size of 180 per arm (figure 1). This sample size will have 80% power to detect the following relative risk changes in secondary outcomes at a significance level of 0.05: PaO_2 _: FiO_2 _ratio (10%); critical care (35%) and hospital (15%) length of stay; HRQL (15%) and breathlessness(20%).

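### Allocation is blocked within centre, but the log-rank test and Cox model are stated without centre: stratifying them is a small, free gain in power for survival

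*Protocol article*

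**What the plan says.** Under Randomisation and drug / placebo supply, the sequence uses blocks of ten with equal allocation, and each patient takes the next numbered pack held at the centre. On supply the article says: "Drug boxes will be supplied in groups of ten to centres thus ensuring an equal allocation between active and placebo groups". The stated purpose is to balance differences in case mix and care between centres.

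Under Statistical analysis plan, the treatment of centre varies by type of outcome:

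- **Primary outcome:** a logistic model with "independent variables as treatment and other important predictors (e.g. centre and age").
- **Other categorical and continuous outcomes:** logistic and linear regression with treatment and further predictors that are not listed.
- **Survival:** "Time to event data will be analysed using a log-rank test". A hazard ratio from a Cox model is also reported. No strata or covariates are stated for either.

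For EQ-5D, Secondary outcomes says: "Data will be collected at baseline, 28 days and 90 days". The linear model that would cover it does not name the baseline value.

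**The concern.** When a design forces balance within centre, part of the chance variation between arms is removed. An analysis that ignores centre does not credit the trial with that removal. Its test then tends to reject less often than the nominal 5% under the null, and it loses power under the alternative. In a Cox model, leaving out a prognostic factor also pulls the hazard ratio towards the null.

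Survival is the one outcome type here whose stated analysis makes no provision for predictors. A plain log-rank test cannot take covariates; centre can enter it only through stratification. At stake is some power for 28- and 90-day survival, both secondary outcomes. The false-positive risk is not raised.

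**Working it through.** **1. The plan's own figure.** Inputs from Power and sample size estimate: "a conservative estimate of the incidence ALI of 25% was selected"; "a treatment effect of at least 12.5% (50% relative reduction) was necessary"; "To demonstrate this effect with 80% power at a significance level of 0.05 will require 336 patients". So p1 = 0.25, p2 = 0.125, difference 0.125, mean 0.1875.

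- Uncorrected n per arm = [1.96·√(2·0.1875·0.8125) + 0.8416·√(0.25·0.75 + 0.125·0.875)]² / 0.125² = (1.0819 + 0.4586)² / 0.015625 = 151.9, so 152 per arm (304 in all).
- With continuity correction: (151.9/4)·[1 + √(1 + 4/(151.9·0.125))]² = 167.5, so 168 per arm, or 336. This matches exactly.
- Allowing for the two losses: 336/(0.95·0.976) = 362.4, close to the stated 360.

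Neither figure depends on how centre is handled in the survival analysis.

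**2. Log-rank test, unstratified against stratified by centre.** From the article: 360 patients, 10 centres, blocks of 10, 1:1. Assumed: equal centres of 36; control 90-day mortality of 10% or 20%; hazard ratio 0.5; normally distributed centre effects on the log hazard with the SD shown. There were 4,000 simulated trials per cell, both tests were applied to the same trials, and each was two-sided at 5%. All results are percentages.

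| Control mortality | Centre SD | Type I: unstratified / stratified | Power: unstratified / stratified |
|---|---|---|---|
| 10% | 0 | 5.1 / 5.2 | 41.3 / 41.0 |
| 10% | 0.3 | 4.8 / 5.0 | 42.0 / 41.9 |
| 10% | 0.5 | 5.0 / 5.4 | 40.6 / 41.0 |
| 10% | 1.0 | 3.4 / 4.6 | 36.6 / 38.9 |
| 20% | 0 | 5.0 / 4.8 | 70.4 / 70.3 |
| 20% | 0.3 | 5.0 / 4.9 | 70.9 / 71.3 |
| 20% | 0.5 | 4.6 / 5.0 | 68.9 / 70.1 |
| 20% | 1.0 | 4.2 / 5.6 | 59.0 / 64.2 |

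The simulation standard error of one power figure is about √(0.41·0.59/4000) = 0.8 points, and of one type I figure √(0.05·0.95/4000) = 0.3 points. Differences of a few tenths should not be read as real. Up to SD 0.5 the largest power gap is 1.2 points. At SD 1.0 the gaps are 2.3 and 5.2 points. Part of the larger gap goes with the stratified test's simulated 5.6% type I error in that cell. With no centre variation, stratifying costs at most 0.3 points.

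**3. Primary outcome, if centre were left out.** N = 360, 25% against 12.5%, 5,000 runs per cell, unadjusted z test against a Cochran-Mantel-Haenszel test by centre. Power is 86.7% against 87.0% at a centre log-odds SD of 0.3, 86.6% against 87.1% at 0.5, and 81.5% against 85.5% at 1.0.

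**4. Baseline EQ-5D.** With correlation ρ between baseline and follow-up, the interval width relative to no baseline adjustment is √(1 − ρ²). The article gives no ρ, so a range is assumed.

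- ρ = 0.3: √0.91 = 0.954, about 5% narrower. A comparison with 80% power rises to Φ(2.80/0.954 − 1.96) = 84%.
- ρ = 0.5: √0.75 = 0.866, about 13% narrower. Power rises to Φ(2.80/0.866 − 1.96) = 90%.

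**The case against.** The strongest reply is that this is a condensed article, and the exact list of covariates is commonly left to the statistical analysis plan, which is not shown. That largely stands for two of the three elements. Centre is the first predictor named for the primary model, so a reader who infers that the primary analysis ignores centre goes beyond the text; the loss in step 3 arises only if a named covariate is dropped. Baseline EQ-5D is unnamed but not excluded: the linear model carries further predictors and reports adjusted means. To say that the plan discards it would be wrong.

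The reply is weaker for survival. There the article names a specific method, and that method as stated does not match the randomisation.

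A second reply is that the gain is negligible at moderate centre variation. That is right. A reader might take the reported incidence of 14.5% to 43% as evidence of strong variation, but it is a range across published reports, not across this trial's centres. Even if it were the spread of ten centres, logit(0.43) − logit(0.145) = 1.49, divided by the expected range of ten normal draws (about 3.08 SD), gives an SD of about 0.48 for lung injury. The documents give no basis for an SD of 1.0.

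A reader might also infer that confidence intervals are too wide throughout. That describes the linear model. In logistic and Cox models, omitting centre mainly pulls the effect towards the null and costs power; adjustment does not narrow the interval on the log scale.

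**Conclusion.** The point holds as a minor efficiency improvement. Randomisation is in effect stratified by centre, and the stated log-rank test and Cox model do not reflect this. The stated analysis remains valid and is at worst conservative: nothing in the documents supports calling it biased or prone to false positives.

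Under the assumed mortality, hazard ratio and equal centres, the loss is about 1 point of power or less for a centre SD up to 0.5. It is about 2 to 5 points at SD 1.0, with type I error of 3.4% to 4.2%. For EQ-5D, naming the baseline value secures an interval about 5% to 13% narrower than one with no baseline adjustment, at an assumed correlation of 0.3 to 0.5. The plan may already intend that adjustment.

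**What to change.** - **Survival:** state that the log-rank test and the Cox model are stratified by centre.
- **Primary logistic model:** make centre a definite term instead of an example. Set a rule in advance for sparse centres: pool very small ones, or use a random intercept if a centre has no events.
- **EQ-5D at 28 and 90 days:** name baseline EQ-5D among the predictors.

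If the full analysis plan already says this, nothing more is needed. Otherwise the cost is a few sentences of wording, with no new data and no change to the sample size.

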### Trial organisation / oversight

Trial oversight will be provided by a Trial Steering Committee (TSC) comprising of investigators, clinicians and trialists. The TSC will operate within the relevant WCTU SOP. An independent data monitoring committee will monitor the safety of participants enrolled in the trial through regular review of adverse event reports. An interim analysis of efficacy is not planned.

## Abbreviations

AE: Adverse event; ALI: Acute lung injury; ARDS: Acute respiratory distress syndrome; BAL: Bronchoalveolar lavage; CRF: Case Report Form; CTU: Clinical Trials Unit; DMEC: Data Monitoring and Ethics Committee; HAPE: High Altitude Pulmonary oedema; ICNARC: Intensive Care National Audit and Research Centre; NSTS: NHS Strategic Tracing Service; OLV: One lung ventilation; SAE: Serious adverse event; SUSAR: Suspected unexpected serious adverse reaction; TSC: Trial Steering Committee; VFD: Ventilator free days; WCTU: Warwick Clinical Trials Unit.
